### Ethics

The study was approved by the local medical ethical committee (METC\11270.haa).

### Treatment program

#### Intervention

Patients will be randomized to either Seeking Safety or to standard CBT. Seeking Safety was originally designed as an integrated model for patients that have both PTSD or trauma-related symptoms and SUD. The treatment manual has recently been translated into Dutch [35]. Seeking Safety consists of 25 structured topics, which can be conducted in group or individual modality. In this study, it will be conducted in group modality. Topics are evenly divided among cognitive, behavioral and interpersonal coping skills, with a goal of helping patients attain safety in their lives. ‘Safety’ is defined as reduction in substance use and destructive behavior, establishment of a network of supportive people and self-protection from dangers associated with the disorders.

There will be one Seeking Safety topic per session for the duration of three months, making it possible for patients to receive 12 topics. The topics to be used are: Safety; PTSD-Taking Back Your Power; When Substances Control You; Grounding; Healing from Anger; Honesty; Taking Good Care of Yourself; Compassion; Red and Green Flags; Asking for Help; Creating Meaning; and Life Choices.

Patients that attend a minimum of 7 sessions will be considered “minimum dose completers” [36]. Every session is conducted according to a fixed structure, starting with a check-in to find out how each patient is doing and both strengths and problems in coping since the last session. Second, a quotation is discussed followed by a discussion of the hand-outs in which the topic of the session is related to the patients’ life. This is also the place where coping skills are shared and discussed. Each session ends with a check-out where patients are encouraged to share one thing they have learned during the session and to formulate a commitment (homework) for the next session. The sessions will be facilitated by one therapist or social worker. The therapists and social workers all received a two-day training in Seeking Safety. Furthermore, all sessions will be videotaped and a random sample of 20% will be selected for review. Thus, quality and adherence will be monitored and ongoing supervision will be provided.

#### Comparison condition

Cognitive Behavioral Therapy (CBT) is an evidence-based cognitive behavioral, manual-based model focused on reducing substance use. It includes relapse prevention and motivational interviewing in which positive reinforcement and enhancing self-efficacy among others, are used to attain behavioral change in the patient [37]. CBT is offered once a week for a period of three months in a closed group.

### Data collection

Patients in both treatment conditions will be assessed identically: at the start of treatment (baseline), at the end of treatment (after three months) and at follow up (six months after start of treatment). Patients will be assessed by research assistants at these time points. Under their supervision patients will fill out most of the questionnaires in an online environment in which the data is linked to their electronic patient file.

### Instruments and outcome

The primary outcome in this study is substance use severity at end of treatment as measured with the EuropASI. This measure will provide a composite score for alcohol and drugs which incorporates the number of days of use in the previous 30 days, amount of money spent on drugs or alcohol, perceived problems and burden of problems associated with substance use. The composite score for alcohol use severity will be used as the primary outcome measure for patients with alcohol use disorder and the composite score for drug use severity will be used for patients with substance use disorder according to the DSM-IV. Secondary outcome measures are the other measures listed below.

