#### Inclusion criteria

Eligible participants for this study are both male and female patients that enter group-based outpatient substance use treatment. They have to be 18 years of age or older and sufficiently fluent in the Dutch language. In this study we will include all patients who have experienced a traumatic event and have trauma-related symptoms. These are assessed by asking the patients whether or not they have experienced a traumatic event, and have a score of at least 40 on the Self-report Inventory for PTSD (SRIP). Furthermore, patients meet current DSM-IV criteria for substance dependence or abuse and have active substance use in the previous 30 days.

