#### Randomization

Randomization will be at patient level. The participants will be randomly appointed to either the control group or the experimental group. The care-takers are blind for this randomization. Envelopes will be distributed to the treatment facility and these contain the questionnaires that will be administered at t = 0. After completing the questionnaires patients will be randomized based on a predefined randomization schedule. Randomization will be performed in blocks of 4 and 8 (in random order). The research assistants that administer the questionnaires for t = 1 and t = 2 will be kept blind for this randomization.

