### Sample size calculation

The sample size for this study is calculated using a significance level of 95% (p < 0.05), a power of 80% and the same number of patients in the intervention and control group (ratio = 1).

Primary outcome variable is substance use severity as measured with the EuropASI. In recent studies, conducted within the same institution [34] but with a population of inpatients, a mean baseline score of 5.2 was found for the alcohol domain and 4.0 for the drugs domain. We expect the mean baseline scores for the outpatients to be somewhat lower, however not considerably. For comparison of baseline scores on the EuropASI, see [22,23]. For practical reasons we are using the mean of both domains (alcohol and drugs) for the sample size calculation. Thus, the mean score for substance use severity will be somewhat lower than (5.2 + 4.0)/2 = 4.6 with a standard deviation of 2.7. For this sample size calculation we will use a baseline score of 4.0 with the same standard deviation. We expect the substance use severity to improve with 60% [23] to 1.6 (SD = 2.0) at end-of-treatment for the intervention group and 2.8 (SD = 2.0) for the control group. We used PS – Power and Sample Size Calculation to calculate the sample size, which resulted in a sample size of 45 patients in each group. Drop-out rates for this treatment are available for the past years from a management information system and are estimated around 20%. This drop-out rate may seem low compared to the numbers that are known from previous studies in SUD patients. However, we will use this percentage to calculate the number of patients that are needed, but will perform an analysis on drop-out halfway through the study. When the drop-out rates turn out to be higher than expected, an amendment will be proposed to the medical ethical committee to continue including patients for an extended period of time. Because of the calculated drop-out rate, an extra 9 participants will be included in both the intervention and the control group, yielding a total of 108 participants for the randomized controlled trial. Based on treatment entry numbers from previous years, approximately two years will be needed to include all patients. Furthermore, this number of patients seems plausible considering sample sizes in previous studies that show similarity in design [21,22].

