### European addition severity index (EuropASI)

The EuropASI is the European adaptation of the fifth edition of the addiction severity index [38]. It is a semi-structured interview that gives a multidimensional profile of the substance-dependent individual and the severity of the addiction. It covers seven main problem areas (medical, employment, alcohol, drug, legal, psychiatric, and family and social) that are most commonly affected by substance abuse. Scoring is based on two indices for each problem area: firstly, the interviewer’s severity rating, in which the interviewer indicates the severity of the patient’s problems and his or her present need for additional treatment on a 9-point scale. Secondly, a composite score (range 0 - 1), an arithmetically based indicator of current (30 day) problem severity, is obtained. Composite scores for the EuropASI are computed with a strategy similar to the one used in the ASI [39].

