### Statistical analyses

All analyses will be executed using SPPS for Windows version 18.0. Frequency tables will be provided for all baseline, end of treatment and follow-up variables. Descriptive statistics will include mean, median, interquartile range, numbers and percentages of patients, as appropriate. If applicable, 95% confidence intervals will be given. To compare differences between groups (Seeking Safety vs CBT) *t*-test or mann whitney U tests will be used in case of continuous variables, as appropriate. For categorical variables chi-squared tests will be used. Repeated measures analyses (mixed models in SPSS) will be used to test the differences between the treatment conditions over time in severity of substance use problems as measured by the EuropASI severity score (pre, post and follow-up). The data will be tested for normality and transformed as appropriate when the data are skewed. Analyses will be based on the intent-to-treat principle. Participants have to attend at least one session to be considered part of this group. Differences regarding gender will be analysed and when appropriate, gender will be included in the analyses as a confounder or effect modifier. Multiple Imputation will be used for missing data. Effect sizes will be calculated to facilitate comparison of improvement between the two groups. Linear regression analyses will be used to determine the predictors of change in substance use and trauma symptoms. Also, amount of prior psychiatric treatment will be used in the analysis as a covariate.

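### The diagnosis rule for the primary outcome overlaps and leaves the value undefined for patients with both alcohol and drug diagnoses, and the sample size rests on a different variable

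*Protocol article*

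**What the plan says.** Instruments and outcome names the endpoint: "The primary outcome in this study is substance use severity at end of treatment as measured with the EuropASI". It then splits the score by diagnosis. The first clause reads "The composite score for alcohol use severity will be used as the primary outcome measure for patients with alcohol use disorder", and the second "the composite score for drug use severity will be used for patients with substance use disorder according to the DSM-IV".

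Inclusion criteria requires that "patients meet current DSM-IV criteria for substance dependence or abuse and have active substance use in the previous 30 days". It does not exclude patients who have both an alcohol and a drug disorder.

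The EuropASI section lists alcohol and drug as separate problem areas. Each has two indices: an interviewer severity rating on a 9-point scale, and "a composite score (range 0 - 1), an arithmetically based indicator of current (30 day) problem severity, is obtained".

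Sample size calculation uses another variable: "For practical reasons we are using the mean of both domains (alcohol and drugs) for the sample size calculation". Its inputs are inpatient baseline means of 5.2 (alcohol) and 4.0 (drugs), a planning baseline of 4.0, and end-of-treatment means of 1.6 and 2.8 with SD 2.0.

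Statistical analyses models change "in severity of substance use problems as measured by the EuropASI severity score (pre, post and follow-up"), without naming a domain.

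**The concern.** A primary outcome should give each patient exactly one value, by a rule that is settled before outcomes are seen. Here the second clause uses a term that the article applies to its whole population, so read literally it contains the first. Reading it as drug use disorder removes the literal overlap but does not help a patient who has both diagnoses, because that patient still meets both clauses.

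Two things are at stake. For patients with both diagnoses, the analysed score can be selected with the data in hand. And the power statement belongs to a variable that is not the primary outcome, so a reader cannot tell what power the trial has for its own endpoint. The first problem also reaches the cost-effectiveness analysis, which takes the primary outcome as its measure of effect.

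**Working it through.** **1. Does the rule give one value per patient?** Reading the second clause as drug use disorder, the most favourable reading:

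| Intake diagnosis | Alcohol clause | Drug clause | Primary value |
|---|---|---|---|
| Alcohol only | met | not met | alcohol composite |
| Drug only | not met | met | drug composite |
| Both | met | met | undefined |

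Read literally, the alcohol-only row also meets the second clause. No section of the article resolves either case. The share of patients with both diagnoses is not given.

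**2. Is the same variable used throughout?**

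| Section | Variable |
|---|---|
| Instruments and outcome | one domain's composite, chosen by diagnosis |
| EuropASI section | composite, range 0–1, one per domain |
| Sample size calculation | mean of both domains; inputs 5.2, 4.0, 1.6, 2.8 |
| Statistical analyses | one EuropASI severity score, domain not named |

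The sample size inputs all exceed 1, so they cannot be composites. They fit the 9-point interviewer rating.

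**3. Does the stated sample size reproduce?** Difference 2.8 − 1.6 = 1.2; SD 2.0; standardised difference 1.2 / 2.0 = 0.6; two-sided alpha 0.05; power 80%. A two-sample t-test needs 44.6, so 45 per group, with 80.4% power at 45. The plan's 45 reproduces. The arithmetic is sound for the variable it used.

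**4. Would that power carry over to a single-domain score?** This needs assumptions that the documents do not supply: that 2.0 is the SD of a patient-level two-domain mean, that both domains have equal SD, and that the difference on the single-domain score is still 1.2. With between-domain correlation r,

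SD of mean = SD of single domain × √((1 + r)/2), so SD of single domain = 2.0 / √((1 + r)/2).

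| Assumed r | Single-domain SD | n per group for 80% | Power at 45 per group |
|---|---|---|---|
| 1 | 2.00 | 45 | 80% |
| 0.75 | 2.14 | 51 | 75% |
| 0.5 | 2.31 | 60 | 68% |
| 0.25 | 2.53 | 71 | 60% |
| 0 | 2.83 | 89 | 51% |

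The r = 0 row is the extreme of this range, not an estimate.

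**5. What does ignoring domain cost by itself?** Take a within-domain SD of 2.0, a difference of 1.2, an alcohol share p of 30–50% and a domain gap g at end of treatment, all on the planning scale. The pooled SD is √(4 + p(1 − p)g²). For g = 0.48–0.72 the SD is 2.01–2.03 and power at 45 is 79–80%. For g = 1.2 it is 2.07–2.09 and 77%. For g = 2.0 it is 2.20–2.24 and 71–73%. The cost is small unless the gap is large.

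**The case against.** The strongest reply is that this is loose wording in a condensed article. For a patient with one diagnosis the natural reading fixes the domain at entry, because the DSM-IV diagnosis is an entry criterion. Averaging the domains for planning is openly called a practical step. Covariates and stratification are commonly left to a full protocol or analysis plan. The first part stands for single-diagnosis patients only. It does not reach those with both diagnoses, and the definition of the primary outcome is something the article does fix.

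Several stronger readings are tempting and are not supported:

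- **A sizeable shift from an unequal alcohol/drug mix.** The gap 5.2 − 4.0 = 1.2 equals the planned effect. With a 50:50 mix, the 95% chance limit for imbalance in alcohol share is 1.96 × √(0.25 × 2/45) = 0.207, and 0.207 × 1.2 = 0.25 points, about 20% of the effect. But these figures are not on the 0–1 composite. They come from inpatients at baseline, and the article does not say that they are alcohol scores in alcohol patients and drug scores in drug patients. Scaled to the planned end-of-treatment means (1.6/4.0 = 0.4 and 2.8/4.0 = 0.7), the gap is 0.48–0.84 and the shift 0.10–0.17, well inside the standard error of the difference, 2.0 × √(2/45) = 0.42.
- **Bias from pooling.** Randomisation makes the comparison unbiased in expectation. Chance imbalance in domain costs precision. Pooling itself is implied by one outcome and one model, not stated.
- **Two different scales.** Both composites run from 0 to 1. They are separately built domain scores on the same nominal range.
- **No stratification by domain.** The Randomization section says "Randomization will be performed in blocks of 4 and 8 (in random order") and refers to a predefined schedule that it does not detail. Silence in an article is not proof.

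The power figures in step 4 are also open to challenge. The article does not say whose SD the 2.0 is. For a patient with one diagnosis, averaging in the other domain could dilute the effect, so the difference on the index domain could exceed 1.2 and power could be higher than the table shows.

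**Conclusion.** The point holds in this form: the primary value is undefined for patients with both alcohol and drug diagnoses, and the stated 80% power has not been shown for the variable named as primary. The first part needs no assumption; it follows from the outcome rule and the eligibility criteria. How many patients it affects is unknown.

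The second part is a gap in justification rather than proof of an underpowered trial. Under the step 4 assumptions, correlations from 0.75 to 0.25 put power at about 75% down to 60% at 45 per group. Those figures illustrate how far the planning variable and the endpoint can diverge; they do not estimate this trial's power. A reader should not infer a biased comparison, or a known shift in points, from an uneven domain mix. The documents give neither the domain gap on the composite nor the correlation between domains.

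**What to change.** 1. Replace the term in the second clause with drug use disorder, if that is what is meant.
2. Fix one index domain per patient before randomisation from the intake DSM-IV diagnosis. State a single baseline rule for patients with both diagnoses, for example the domain with the higher baseline composite after standardising within domain.
3. Use that domain at every visit, and include index domain and baseline score as covariates.
4. Report the non-index composite as a secondary outcome, so that a move from one substance to another is visible.
5. Name the same index (composite or severity rating) in the outcome, sample size and analysis sections, and restate the sample size assumptions and power for that variable on its own scale.

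The cost is mostly wording. The diagnosis is already needed for entry and the baseline EuropASI is already collected before randomisation. The example rule requires the baseline interview to be scored, and reference SDs to be fixed, before allocation. Choosing the higher baseline score also brings some regression to the mean, which is expected to be equal in both arms. The analysis takes slightly more work, and the restated power may be lower or less certain than 80%.

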### European addition severity index (EuropASI)

The EuropASI is the European adaptation of the fifth edition of the addiction severity index [38]. It is a semi-structured interview that gives a multidimensional profile of the substance-dependent individual and the severity of the addiction. It covers seven main problem areas (medical, employment, alcohol, drug, legal, psychiatric, and family and social) that are most commonly affected by substance abuse. Scoring is based on two indices for each problem area: firstly, the interviewer’s severity rating, in which the interviewer indicates the severity of the patient’s problems and his or her present need for additional treatment on a 9-point scale. Secondly, a composite score (range 0 - 1), an arithmetically based indicator of current (30 day) problem severity, is obtained. Composite scores for the EuropASI are computed with a strategy similar to the one used in the ASI [39].

### Obsessive compulsive drinking scale (OCDS)

The OCDS is a quick and reliable self-rating instrument that provides a score that measures cognitive aspects of craving of alcohol or drugs during the past seven days [40]. The short version of the scale [41] that is used in the current study consists of 5 items which can be scored on a 0-4 scale, where a higher score indicates higher obsessions and compulsions regarding drugs or alcohol.

### Self report inventory PTSD (SRIP)

The SRIP is a self-report measure of PTSD [42]. The duration of this measure is five minutes, which makes it very time-efficient. The SRIP contains 22 items, based on the DSM-IV-TR criteria for PTSD. The items are scored on a 4-point Likert scale, varying from 1 ‘not at all’ to 4 ‘often’, and indicates the intensity of the PTSD-symptoms in the past month. A total-score of 52 or higher indicates a PTSD-diagnosis. The SRIP uses the three subscales described in de DSM-IV-TR criteria: ‘Intrusion’, ‘Avoidance’, and ‘Hyper arousal’. Besides this, the 22 items are subdivided in four factors: ‘Emotional numbing’, ‘Avoidance’, ‘Intrusion’, and ‘Sleeping problems’. The test does not contain trauma-specific items, therefore the SRIP is suitable for any population. Research provides evidence for a high reliability of this measure. Hovens [43] found, with the Clinician Administered PTSD Scale (CAPS) [44] as criterion, an internal consistence reliability of the total score between .90 and .94.

### Trauma symptom checklist (TSC-33)

The TSC-33 is a research measure that evaluates symptomatology in adults associated with childhood or adult traumatic experiences. It measures aspects of posttraumatic stress and other symptom clusters found in some traumatized individuals. It does not measure all 17 criteria of PTSD, and should not be used as a complete measure of that construct [45]. It is included in the current study to measure the aspects of psychological effects of traumatic experiences in addition to the standard DSM-IV criteria of PTSD.

### Utrecht coping list (UCL)

The UCL [46] is a self-report instrument to measure the way people deal with problems or stressful situations. The questionnaire consists of 47 items divided into 7 subscales measuring seven different coping strategies: 1. ‘Active problem solving’, 2. ‘Palliative responses’, 3. ‘Avoidance and passive expectancy’, 4. ‘Seeking social support’, 5. ‘Depressive reaction pattern’, 6. ‘Expressing emotions’ and 7. ‘Comforting cognitions’. Each item can be answered with ‘seldom or never’, ‘sometimes’, ‘often’ and ‘very often’. A total score is obtained by adding the scores of all items together.

It is important to note, that although Seeking Safety emphasizes coping skills, we do not expect the scores of all patients to improve on every subscale of the UCL. Some of the ideas behind Seeking Safety are actually aimed at helping patients to avoid certain situations or feelings. This is not considered to be good or bad. The purpose of this study is to explore changes in coping styles and relate these changes to Seeking Safety.

### EuroQol-5D (EQ-5D)

For the overall quantification of health status as a single index we will use the standard EQ-5D classification system developed by the EuroQol Group [47]. The EQ-5D is one of the three widely used multi-attribute systems available to determine health state preferences (utilities). The EQ-5D classification describes health status according to five attributes (five questions): mobility, self-care, usual activities, pain/discomfort and anxiety/depression. Each attribute has three levels, i.e., ‘no problems’ (1), ‘some problems’ (2) and ‘severe problems’ (3). Health state descriptions are constructed by taking one level for each attribute (e.g., 11111 represents the highest health status). Theoretically this set of attributes and the levels of the EuroQol-5D instrument allow for 243 (35) different health-status descriptions. Based on the descriptive classification of the EQ-5D system a preference index (utility) can be estimated that expresses the overall preference of the classified health status. These utility figures are required to calculate Quality-Adjusted Life Years (QALYs) for the cost-utility analysis [48].

